### Secondary Endpoints: FSS, FAS, K-PHQ-9, Pattern Identification

The FSS is a 9-item, self-reported screening tool developed by Krupp et al [26] that assesses fatigue over the past week on a scale of 1 to 7 per item, with higher total scores indicating higher levels of fatigue. The FAS is a 10-item, self-reported screening tool developed by Michielsen et al [27] that examines the psychometric qualities due to fatigue on a scale from 1=“Never” to 5=“Always” per item, with a higher total score indicating higher levels of the psychological impact of fatigue. The PHQ-9, developed by Kroenke et al [28] was validated in the Korean version [29]. It comprises 9 items in total. Respondents rate the frequency of symptoms on a scale of 0-3 per item, with a total score of 10 or higher indicating major depression. These secondary endpoints will assess the clinical effectiveness of HH333 on poststroke fatigue and depression. Pattern identification is a unique diagnostic system in Korean medicine, and the diagnosis of stroke is based on 4 patterns which are fire heat, Dampness-phlegm, Qi deficiency, and Yin deficiency [30]. Jung et al [31] developed an equation model that predicts the probability of each pattern identification diagnosis given variables for stroke pattern identification and is being used for Korean medicine's standardized diagnosis of patients with stroke. Using a stroke pattern identification prediction model, the change in each pattern identified after HH333 administration was collected to obtain data for stroke treatment in Korean medicine. Investigations were conducted during the administration period on days 0 (baseline), 90, 180, 270, 360, 450, 540, 630, and 720.

### Exploratory Endpoints: K-NIHSS, mRS, K-mBI, and K-MoCA

The NIHSS is a tool for assessing neurological deficits resulting from stroke developed by the National Institutes of Health [32] and is currently the most widely used tool for stroke severity assessment, with a Korean version validated and used [33]. It comprises 15 questions in 11 checkpoints, each of which is scored on a scale of 0 to 4, with a total score calculated, with higher scores indicating higher severity. The mRS is a tool developed by van Swieten et al to assess the degree of disability in patients with stroke [34] and is currently the most widely used stroke functional assessment scale [35]. It is rated on a scale of 0 to 6, with higher scores indicating more severe impairment. The mBI is a tool to assess independence in activities of daily living after stroke developed by Shah et al [36], and translated with validation in Korean [37]. It contains 10 questions, each rated on a scale of 0 to 5, 0 to 10, or 0 to 15, with a higher total score indicating a lower dependency. The MoCA is a tool that examines cognitive function and was originally developed to identify mild cognitive impairment [38] but is now widely used for cognitive impairment caused by stroke, and the Korean version has been validated and used [39]. It consists of visuospatial and executive (5 points), naming (2 points), attention (6 points), language (3 points), abstraction (2 points), delayed recall (5 points) and orientation (6 points). The perfect score is 30, with a higher total score indicating higher cognitive function. Investigations were conducted during the administration period on days 0 (baseline), 90, 180, 270, 360, 450, 540, 630, and 720.

### Safety Assessments and Monitoring

At each visit, participants will be screened for adverse events, laboratory tests, urine findings, electrocardiograms, hemorrhagic events such as cerebral hemorrhage or gastrointestinal bleeding related to antiplatelet or anticoagulant use, vital signs, and physical examinations. Laboratory findings included complete blood count (red blood cells, hemoglobin, hematocrit, platelets, and white blood cells) and biochemistry (fasting blood sugar, blood urea nitrogen, creatinine, natrium, potassium, chloride, aspartate aminotransferase, alanine aminotransferase, C-reactive protein, calcium, and uric acid). Urine findings included specific gravity, pH, albumin or protein, glucose, ketone, bilirubin, occult blood, urobilinogen, nitrite, leukocytes, and human chorionic gonadotropin in women of childbearing age. Adverse events included both self-reported symptoms and those judged by the investigator and were collected until 30 days after the end of administration.

After collecting all adverse events that appeared as test findings and symptoms in each group, we compared the frequency and severity of adverse events between the groups and their relationship with the study medications. Adverse events that are not related to the study medications do not meet the criteria for dropout but allow the patient to receive the best possible care regardless of the study. If SAEs occur, the study will be stopped immediately, in part or in whole, and the study researcher will report it to the principal investigator and the institutional review board for appropriate action.

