Experiment medication administration		✓	✓	✓	✓	✓	✓	✓	✓	✓	✓		
Medication adherence^i^			✓	✓	✓	✓	✓	✓	✓	✓	✓		If needed
Concomitant treatment		✓	✓	✓	✓	✓	✓	✓	✓	✓	✓	✓	If needed
Primary efficacy endpoint: recurrence of ischemic stroke			✓	✓	✓	✓	✓	✓	✓	✓	✓	✓	If needed
Secondary efficacy endpoints^j^		✓		✓	✓	✓	✓	✓	✓	✓	✓		If needed
Exploratory endpoints^k^		✓		✓	✓	✓	✓	✓	✓	✓	✓		If needed
Safety assessments^l^			✓	✓	✓	✓	✓	✓	✓	✓	✓		If needed
Adverse events^m^		✓	✓	✓	✓	✓	✓	✓	✓	✓	✓	✓	

^a^Telephone investigation.

^b^UV: Unscheduled visit. Visiting on a day other than the original visit schedule due to an adverse event, etc.

^c^Screening performed within 14 days of informed consent.

^d^Age, sex, smoking, and alcohol history.

^e^Within 1 year prior to visit 0.

^f^Time of first onset and diagnosis (including year, month, and day if possible), date of computed tomography or magnetic resonance imaging, ischemic stroke territory, Trial of Org 10172 in Acute Stroke Treatment classification, history of stroke-related surgery, stroke risk factors, and stroke-related symptoms.

^g^Within 4 weeks prior to visit 0.

^h^Complete blood count (red blood cell, hemoglobin, hematocrit, platelet, white blood cell); biochemistry (fasting blood glucose, blood urea nitrogen, creatinine, natrium, potassium, chloride, aspartate aminotransferase, alanine aminotransferase, C-reactive protein, calcium, uric acid); urine human chorionic gonadotropin for women of childbearing age, excluding sterilization and menopause (more than 12 months since last menstrual period); premature menopause before the age of 40 years, follicle-stimulating hormone test for differential diagnosis.

^i^Drop out if <80%.

^j^Total scores of Fatigue Severity Scale (FSS), Fatigue Assessment Scale (FAS), Korean Patient Health Questionnaire (K-PHQ-9), and probability of each type of Pattern Identification (fire heat, dampness-phlegm, Qi deficiency, and Yin deficiency).

^k^Total scores of the Korean National Institutes of Health Stroke Scale (K-NIHSS), Korean modified Rankin Scale (K-mRS), Korean modified Barthel Index (K-mBI), Korean Montreal Cognitive Assessment (K-MoCA).

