^l^Complete blood count (red blood cell, hemoglobin, hematocrit, platelet, white blood cell); biochemistry (fasting blood glucose, blood urea nitrogen, creatinine, natrium, potassium, chloride, aspartate aminotransferase, alanine aminotransferase, C-reactive protein, calcium, uric acid); urine tests (specific gravity, pH, albumin or protein, glucose, ketone, bilirubin, occult blood, urobilinogen, nitrite, leukocyte, human chorionic gonadotropin for women of childbearing age); electrocardiogram; hemorrhage events (cerebral hemorrhage, gastrointestinal bleeding, etc) related to antiplatelet or anticoagulant; vital sign; physical examination.

^m^Self-reported by the participant or judged by the investigator.

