**Dropout criteria**
If the researcher determines that it is not appropriate for the study to continue according to the dropout criteria, the researcher may stop the treatment and evaluation and drop the participant. Participants may also drop out of the study at any time of their free will. The dropout criteria were as follows:Found not to meet inclusion or exclusion criteria after screening.Patients or caregivers withdraw consent during the study period.Patients or caregivers request to discontinue the study or refuse treatment during the study.Participants cannot be traced.According to the judgment of the investigator, the patient is no longer able to participate in the study because of adverse events or comorbidities.Study medication compliance <80%.Participation in another clinical trial.Judged by the investigator as unfit to continue the study for any other reason.

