### Interventions

HH333 or placebo capsules (one dose: 2 capsules, 800 mg) will be orally administered with water once a day on an empty stomach after waking for 720 days. HH333 is an herbal medicine manufactured by Kyungjin Pharmaceutical Co, Ltd. (Icheon, Republic of Korea). It is a capsule formulation derived from 80% ethanol extracts of *Scutellariae radix, Coptidis rhizoma, Phellodendri cortex, Gardeniae fructus*, and *Rhei rhizoma* (Table 2). The placebo was a capsule manufactured by Kyungjin Pharmaceutical Co., Ltd. (Icheon, Republic of Korea) with the same appearance as HH333.

**Table 2 table2:** Composition of HH333.

Constituent herbs	Scientific names	Weight (g)	
*Scutellariae radix*	*Scutellaria baicalensis* Georgi (from Republic of Korea)	0.28	
*Coptidis rhizoma*	*Coptis japonica* Makino (from Republic of Korea)	0.28	
*Phellodendri cortex*	*Phellodendron amurense* Ruprecht (from Republic of Korea)	0.28	
*Gardenia fructus*	*Gardenia jasminodes* Ellis (from Republic of Korea)	0.28	
*Rhei rhizoma*	*Rheum palmatum* L. (from Republic of Korea)	0.07	
Total			1.2

Medication compliance will be recorded in patients taking either HH333 or placebo. The participants will be instructed to return the empty containers of study medications taken and the remaining medications at each visit to count the actual number of doses of study medications. Compliance was calculated as follows:

If compliance was less than 80% at any point during the study, the participant was excluded from the study

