### Primary Endpoint: Recurrent Ischemic Stroke

Recurrent ischemic stroke within 750 days while taking the study medication was investigated. Recurrent ischemic stroke is defined as a new neurological finding supported by new imaging findings. New neurological findings corresponded to the sudden onset of neurological symptoms identified on neurological examinations that did not occur prior to study participation. New radiological findings are abnormal findings on brain imaging (computed tomography or magnetic resonance), which can explain new neurological findings that did not exist before study participation. The investigation will be conducted on days 30, 90, 180, 270, 360, 450, 540, 630, 720, and day 750, which is 30 days after the end of administration.

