### Statistical Analysis

All statistical analyses were two-sided with a 5% significance level. The statistical program SAS (version 9.4 or more, SAS Institute) was used for the analysis. If at any point there are missing values or participants are dropped before the end of the study, the data will be treated as missing data. All data obtained from the participants were analyzed in 3 forms: full analysis set, per-protocol set, and safety set. Efficacy analysis will be conducted using the results of the full analysis set as the main analysis, and a per-protocol set analysis will be conducted separately to evaluate whether there are differences from the full analysis set results. Safety analysis was performed on the safety set and the safety of the study medications was evaluated. The full analysis set includes all data from participants with at least one efficacy assessment at the primary outcome after taking the study medication. The per-protocol set included participants who were eligible for full analysis and successfully completed the study. The safety set included all data from participants who received at least one dose of the study medication.

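### Dropout rules can end adverse event follow-up before an early stopper's 30-day post-treatment window has passed, although that participant stays in the safety set

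*Protocol article*

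**What the plan says.** All references are to the protocol article.

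- **Collection rule** (Safety Assessments and Monitoring): adverse events "were collected until 30 days after the end of administration". The sentence is not confined to people who finish the course.
- **Schedule** (Study Design, Table 1): dosing lasts 720 days. The adverse event row is ticked at visits 1 to 11. Visit 11, a telephone contact on day 745–755, is the only visit placed after treatment. The primary endpoint section ties it to the planned course: "day 750, which is 30 days after the end of administration".
- **Dropout** (Textbox 1, Dropout criteria): when a criterion is met, "the researcher may stop the treatment and evaluation and drop the participant". One criterion is the investigator's judgement that "the patient is no longer able to participate in the study because of adverse events or comorbidities".
- **Compliance** (Interventions): "If compliance was less than 80% at any point during the study, the participant was excluded from the study". Table 1 note i also makes compliance under 80% a ground for dropout.
- **Safety set** (Statistical Analysis): "The safety set included all data from participants who received at least one dose of the study medication".
- **Other routes to an event** (Table 1, notes b and m): an unscheduled visit is explained as "Visiting on a day other than the original visit schedule due to an adverse event, etc", and adverse events are "Self-reported by the participant or judged by the investigator".

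**The concern.** The collection rule promises every treated participant a safety window after dosing ends. The schedule delivers that window at a fixed calendar point that suits only those who dose to about day 720. For the rest, the article gives the researcher permission to end evaluation and prescribes exclusion for low compliance. Neither provision separates stopping the capsules from ending safety follow-up. The participant nonetheless remains in the denominator of the safety comparison.

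The people concerned are of particular interest for safety. The safety section says that adverse events unrelated to study medication are not grounds for dropout, so participants dropped for an event would tend to be those whose event was thought related. Whether such an event resolved, worsened or was followed by another after stopping would then depend on the researcher's choice and on the participant coming forward. At stake is the completeness of adverse event ascertainment in early stoppers. The efficacy analysis and the sample size are not affected.

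**Working it through.** **1. Does visit 11 deliver the 30 days for completers?** Inputs: last dose on day 720 (Interventions); visit 11 on day 745–755 (Table 1).

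- Nominal: 750 − 720 = 30 days.
- Window: 745 − 720 = 25 to 755 − 720 = 35 days.

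Yes. Completers are not part of this point.

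**2. Does anything in the schedule deliver it for an early stopper?** No visit is tied to the individual's last dose, so coverage depends on when the person stops and on whether evaluation continues.

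- Last dose on day 180: the 30-day point is day 210. Visit 5 (day 255–285) comes 255 − 180 = 75 to 285 − 180 = 105 days after the last dose. Visit 11 comes 745 − 180 = 565 to 755 − 180 = 575 days after it.
- Last dose on day 150: visit 4 (day 165–195) comes 165 − 150 = 15 to 195 − 150 = 45 days after, so it may serve.

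In both cases the later visit takes place only if the participant is still being evaluated. If so, events can also be recorded in retrospect, and little is lost. The weak point is therefore the rule on ending evaluation, not the spacing of visits.

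**3. What do the dropout rules do?** Set side by side:

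| Rule | Force | Effect on follow-up |
|---|---|---|
| Dropout criteria | Permission | Evaluation can end together with treatment |
| Compliance under 80% | Unconditional as worded | Participant leaves the study; adverse event collection is not mentioned |
| Safety set | Unconditional | Participant stays in the safety analysis |

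The compliance formula does not appear in the text available. If it divides doses taken by doses due to date (an assumption), someone who stops on day 180 stands at 180/255 = 71% on the earliest day of visit 5. The compliance rule could then remove that person even where the researcher had chosen to continue evaluation.

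**4. Does the answer depend on how the end of administration is read?** If the 30 days run from the individual's last dose, steps 2 and 3 apply. If they run from the planned end of dosing, as the primary endpoint section might suggest, collection should continue to day 750 for everyone. For a stop on day 180, up to 750 − 180 = 570 days could then be cut short by the same dropout rules. The gap exists on either reading.

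**5. How many participants?** The plan's own figures (Sample Size): 106 per group before dropout; 106 / 0.90 = 117.8, rounded up to 118 per group, 236 in total. This reproduces the stated numbers. The dropout allowance is 236 − 212 = 24 participants from all causes, including withdrawn consent and loss of contact. It is a planning assumption about dropout. It does not count lost windows or missed events.

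**The case against.** The strongest reply is that the collection rule is already right and, read plainly, covers early stoppers. The dropout clause is only a permission. The compliance clause never says that adverse event collection ceases. Unscheduled visits exist, and the investigator already knows about anyone stopped for an adverse event. A condensed article would normally leave an early-termination call to the full protocol, which is not shown.

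Much of this stands. There is no flat contradiction, and the full protocol may hold a safety call. What remains is that the article does state the dropout and exclusion rules, and those rules, followed as written, can work against its collection rule. The unscheduled visit is prompted by an event and not by stopping medication, and Table 1 has no adverse event entry in that column.

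Three stronger readings should be set aside:

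- **That early stoppers will lose the window.** The wording allows the loss but does not require it.
- **That visit spacing measures the gap.** If evaluation continues, later visits can pick up events in retrospect. If it ends, the spacing is irrelevant. The proportion of possible stopping days with no visit about 30 days later therefore sizes nothing.
- **That laboratory deterioration after stopping, such as liver enzymes, is missed in stoppers but caught in completers.** Visit 11 is a telephone contact with no safety assessments ticked, so completers have no scheduled post-treatment laboratory tests either, and a call would not detect such changes.

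**Conclusion.** The point holds as a possibility that the text leaves open: for participants who stop early, the stated dropout and compliance rules can end follow-up before the stated 30 days have passed, while the safety set keeps those participants in. Severity is low, because this is a cheap improvement and not a flaw that threatens the trial.

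Its size cannot be computed from the article. About 24 of 236 is the all-cause dropout allowance; the avoidable part is smaller than the number who drop out, because nobody can follow those who withdraw consent or cannot be traced. A reader might infer a biased comparison between arms. The documents do not show one: the trial is double-blind, and nothing indicates that stopping, or the reasons for it, would differ by arm. The conclusion assumes that the article reproduces the dropout and compliance rules faithfully and that no safety call elsewhere in the full protocol already overrides them.

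**What to change.** 1. In the dropout criteria and in the compliance paragraph of Interventions (with Table 1 note i), state that meeting a dropout criterion, or falling under 80% compliance, ends study medication but not adverse event follow-up.
2. Add a footnote to Table 1 for a telephone safety contact at last dose + 30 days (±5) for every participant who stops early, still consents and can be traced. Visit 11 and the day-750 recurrence check stay as they are.

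If the full protocol already provides such a contact, stating it in these places is enough.

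**Cost:** a wording amendment and one extra call per such participant, at most about 24 calls under the planned 10% dropout and more if dropout is higher. If calls were paid like visits at the stated ₩50,000 (an assumption), 24 × 50,000 = ₩1,200,000; if they are unpaid, there is no participant payment. Only 12 participants had been randomized by November 13, 2024, so a prompt amendment would still reach most of the trial.

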### Safety Analysis

An adverse event is a new occurrence of a symptom after study medication administration that was not observed before administration and includes unintended consequences such as abnormal laboratory findings, symptoms, and temporary events related to the study medications. The severity of adverse events, both self-reported and non–self-reported, will be assessed by the investigator by applying Spilker’s classification as follows: mild, not requiring additional intervention, nor significantly inhibiting the normal lifestyle (function) of the participant; moderate, significantly inhibiting the normal lifestyle (function) of the participant and may need additional intervention, recovering afterward; severe, severe adverse events requiring intensive intervention; and leaving sequelae. The causal relationship between adverse events and the study medication will be assessed by the investigator using the following six-level grading scale: (1) definitely related, (2) possibly related, (3) probably related, (4) not related, (5) definitely not related, and (6) unknown.

For all adverse events and abnormal findings on examination, the symptoms, frequency, and degree of relationship with the study medication were recorded in detail for each group. The number and proportion of participants in whom adverse events occurred at least once, 95% CI, and number of occurrences within each group will be presented. Differences in proportions between groups will be tested using the chi-square test or Fisher exact test.

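### The SAE stopping rule has no exemption for recurrent ischemic stroke or unrelated events, so the primary endpoint itself would very probably trigger it

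*Protocol article*

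**What the plan says.** Safety Assessments and Monitoring gives the rule: "If SAEs occur, the study will be stopped immediately, in part or in whole". The same sentence sends the event to the principal investigator and the institutional review board for them to act on. The sentence before it deals with dropout: "Adverse events that are not related to the study medications do not meet the criteria for dropout".

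Safety Analysis defines the events in scope: "An adverse event is a new occurrence of a symptom after study medication administration that was not observed before administration". The section on the primary endpoint defines recurrence as a new neurological finding with supporting imaging, and explains the first part: "New neurological findings corresponded to the sudden onset of neurological symptoms identified on neurological examinations that did not occur prior to study participation".

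Four other places bear on what happens next:

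- The dropout criteria in the Eligibility textbox say that, where continuing is judged inappropriate, "the researcher may stop the treatment and evaluation and drop the participant". One criterion, left to the investigator's judgment, is that "the patient is no longer able to participate in the study because of adverse events or comorbidities".
- The dropout criteria, the Interventions section and Table 1 (footnote i) all remove a participant whose compliance falls below 80%.
- Table 1, footnote b, provides for unscheduled visits: "Visiting on a day other than the original visit schedule due to an adverse event, etc". Endpoints are assessed at these visits if needed.
- Statistical Analysis says that if "participants are dropped before the end of the study, the data will be treated as missing data".

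**The concern.** The stop is mandatory and immediate, and its only condition is that SAEs occur. Relatedness, expectedness and number play no part. A recurrent stroke is a new symptom after dosing, so it is an adverse event under the article's own definition, and a serious one is an SAE. No section exempts it. The trial therefore has a safety rule that fires on the event it was set up to count.

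An unrelated SAE falls under two adjacent sentences that point in different directions. It is no ground for dropout, yet it stops the study at least in part. Three sites have to apply this without being told what a partial stop covers. At stake are whether the trial can run to its planned number of events and, to a lesser degree, whether outcome data after an SAE are kept.

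**Working it through.** **Inputs.** From Sample Size: 24-month recurrence of 12.5% to 12.8% on control and 1.7% on HH333; 106 per group before dropout and 118 after. From Statistical Analysis: two-sided 5% level. The article does not define SAE, so the share s of recurrences that are serious is an assumption, taken from 10% to 100%.

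**1. The plan's own figure.** The two-proportion formula at 12.5% vs 1.7%, 80% power, two-sided 5%, gives 88 per group without continuity correction and 106 with it. Allowing for 10% dropout, 106/0.9 = 117.8, so 118. Both stated figures reproduce, and the sample size is not in question.

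**2. Expected recurrences, n × (control rate + HH333 rate).**

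- 106 per group: 106 × 0.142 = 15.1 and 106 × 0.145 = 15.4.
- 118 per group: 118 × 0.142 = 16.8 and 118 × 0.145 = 17.1.

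**3. Chance that the endpoint triggers the rule.** P(at least one serious recurrence) = 1 − [(1 − 0.125s)(1 − 0.017s)]^106.

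| s (assumed) | expected serious recurrences | P(at least one) |
|---|---|---|
| 10% | 1.5 | 78.0% |
| 25% | 3.8 | 97.8% |
| 50% | 7.5 | 99.96% |
| 100% | 15.1 | >99.99% |

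The chance reaches 95% at s = 19.7% (17.7% with 118 per group).

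**4. Whole-study reading.** With 118 per group and no events on HH333, Fisher's exact test gives p = 1.0 at 1 control event and p = 0.060 at 5. It first falls below 0.05 at 6 (p = 0.029). The chance that the first serious recurrence is among the first five recurrences is 1 − (1 − s)^5: 41% for s = 10%, 76% for 25%, 97% for 50% and 100% for 100%. Unless few recurrences are serious, a stop for good at the first serious one would usually come before even the most favorable split could reach significance.

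**5. Partial reading.** If only study medication is held and visits continue, the rule itself loses no outcome data. If a site instead ends evaluation:

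- *After a recurrence* the binary primary outcome is already known, so only later scores are lost. There are 8 post-baseline score visits, so 118 × 8 = 944 per group. With recurrence times uniform over 720 days, 4.5 score visits follow a recurrence on average, or 3.5 if scores are taken at the detecting visit.
  - Worst case, s = 100%, control: 118 × 0.125 = 14.75 recurrences; × 3.5 = 51.6 and × 4.5 = 66.4 visits, or 5.5% to 7.0% of 944.
  - Worst case, s = 100%, HH333: 118 × 0.017 = 2.006 recurrences; 7.0 to 9.0 visits, or 0.7% to 1.0%.
  - At s = 25%: 1.4% to 1.8% vs 0.2%.
- *After a non-stroke SAE* follow-up for the primary endpoint is cut. The article gives no rate for these. If a share q of participants stop, losing half of follow-up on average, the recurrences unseen are (q/2) × 16.76: 0.08 at q = 1%, 0.42 at 5% and 1.68 at 20%, out of about 17.

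**The case against.** The strongest reply is that the sentence is graded. It allows a partial stop and sends the event for review, so it need not halt the trial at the first SAE. This stands. A reader might infer that the protocol requires such a halt, but the text does not say so, and it does not say that a stop is permanent. What remains is that the stop comes before the review and that its scope is left open.

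A reader might also infer that each SAE ends follow-up and biases the primary analysis. The documents do not support that. The pairing of treatment with evaluation comes from the dropout criteria, where it is something the researcher may do. Unrelated adverse events are expressly no ground for dropout, Table 1 allows unscheduled visits, and after a recurrence the primary outcome is already recorded. Even in the worst case the lost score visits total 59 to 75 of 1,888 (3.1% to 4.0%). The imbalance of about 7 to 1 (0.125/0.017 = 7.4) exists only if the planned effect is true, and no resulting bias in any score has been estimated.

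The opposite inference, that a medication hold costs nothing, is not safe either. A long hold could bring compliance below 80% and lead to dropout under a separate rule.

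Finally, the full protocol may define SAE and describe how endpoint events are handled. That is why a missing definition is not part of this point. The rule that the article does state is unconditional, and nothing in the article qualifies it.

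**Conclusion.** The point holds as a badly worded rule. At the planned rates the primary endpoint would very probably trigger it: 78% if one recurrence in ten is serious, above 97% if a quarter or more are. These figures rest on the Sample Size rates and the assumed serious share.

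The consequence depends on the reading. A stop of the whole study for good would probably leave the question unanswered unless few recurrences are serious. A partial stop has an effect that turns on what is stopped, and the expected data loss is small and conditional. The text forces neither a trial-wide halt nor loss of follow-up. Severity is minor to moderate.

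**What to change.** Reword the rule in Safety Assessments and Monitoring so that:

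1. a protocol-defined recurrent ischemic stroke, or an SAE unrelated to study medication, is recorded and reported but does not by itself stop the study;
2. an SAE may stop that participant's study medication;
3. any halt of the trial is decided after review by the principal investigator and the institutional review board.

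In the dropout criteria and the Interventions section, state that stopping medication, including a hold that takes compliance below 80%, does not end outcome visits where the participant agrees. Recurrence would then be followed to day 750 and the scores to day 720, as already scheduled.

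The cost is a wording amendment with notice to the institutional review board, plus keeping already scheduled visits for participants who are off medication. Sample size and visit schedule do not change. The Results section reports 12 participants randomized by November 13, 2024, so at that date most of the 236 were still to be enrolled.
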